#### Evaluating impact on service utilisation

We will conduct an interrupted time series study to evaluate the impact of the detection component (case-finding, diagnosis, referral, and engagement) of the psychosis detection and management system on service utilisation. Following the HSA screening assessment, people with probable psychosis will be referred to the appropriate facility in the care pathway, depending on severity. We will establish a simple, paper-based, case registration system in all the potential referral facilities, including private sector facilities, at least three months prior to initiating case-finding in that district. This will create sufficient baseline data time points in the pre-intervention period to allow us to assess levels of service utilisation for people with psychosis (new and existing) prior to the intervention and during the implementation of the detection system. This method has been used previously in Malawi to investigate the impact of an intervention on general mental health contacts with facilities [14]. We will use segmented linear regression using aggregated monthly utilisation data to assess whether the detection system leads to a significant increase in utilisation of each type of service beyond pre-intervention trends [39].

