*What is the feasibility of the psychosis management and detection system in Salima and Chiradzulu*?	ToC workshops 3 and 5 (n = 20 per district)	PWLE Family/caregivers Traditional Healers Religious Healers	HSAs PHC staff DMHT staff Government representatives
	Survey methods (n = 40)		HSAs
	Feasibility testing	People with possible psychosis (n = 20)	HSAs (n = 10)

Key: PCHC = Primary Care Health Centre; DMHT = District Mental Health Team

The first WP2 ToC workshop (ToC 3 overall) will review our understanding of the ToC Roadmap, review the draft manual, and consider the implementation strategies that will be needed to successfully deploy the intervention.

The second WP2 ToC workshop (ToC 4 overall) will include healthcare colleagues only, considering the healthcare elements of the intervention, to review the implications of the draft manual for the delivery of current services, and to develop feasibility and fidelity-to-manual measures. The third and final ToC of WP2 workshop (ToC 5 overall) will consider the final prototype manual and procedures alongside the feasibility testing data.

Given the HSAs are the group of professionals we are focussed on in this programme, their views of the draft manual and procedures will be critical. We will qualitatively and quantitatively re-survey 40 HSA’s (from those surveyed in WP 1). This is also two-thirds of the cohort of HSA’s who will be involved in the roll-out of the approach in WP3. This continuity reinforces the innovation pathway, by strengthening engagement with this group of professionals through early sight of draft materials and facilitating co-production via shared perspectives—thus shaping the final prototype manual and materials.

We will train 10 HSA’s in one of the two districts in WP1, in both the urban and rural setting, to use the draft manual and procedures to set up the first deployment of the approach. This will also require the training of Primary Care Health Centre and District Mental Health Team staff in the psychosis detection and management system, and in particular to support and supervise HSAs. This approach will then be ‘beta-tested’ within the regular working day of HSAs for two months to test it in practice. Any challenges will be logged in a risk register and solutions found with the Community Advisory Board. We plan to conduct feasibility testing on 20 people with possible psychosis, referred to them through the community or from healthcare staff.

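### A guaranteed baseline of three monthly points is called sufficient for the WP3 interrupted time series, but cannot support its test of an increase beyond the pre-intervention trend

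*Protocol article*

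**What the plan says.** The section Evaluating impact on service utilisation (Protocol article, WP3) bases the series on a register created for the study: "We will establish a simple, paper-based, case registration system in all the potential referral facilities". It is to open "at least three months prior to initiating case-finding in that district. This will create sufficient baseline data time points in the pre-intervention period". The purpose given for that baseline is to assess levels of service use before and during implementation.

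The analysis is "segmented linear regression using aggregated monthly utilisation data", used to judge whether the detection system "leads to a significant increase in utilisation of each type of service beyond pre-intervention trends". The support offered is earlier use of the method in Malawi. The section gives no number of points, expected change or precision.

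Two other places bear on this. Table 3 lists a review of district health data for the service-use question, without a look-back period. The WP2 section trains 10 HSAs "in one of the two districts in WP1, in both the urban and rural setting, to use the draft manual and procedures". It also calls for training of health-centre and district team staff, followed by two months of live use with about 20 people. Both WP1 districts return in WP3, where roll-out goes one district at a time.

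**The concern.** The baseline is declared adequate for describing a level and is then used to test against a trend. A departure from trend is measured from the pre-intervention line projected forward, and only pre-intervention points inform that line's slope. Three of them give a very imprecise slope, and they cannot show curvature or a seasonal pattern. Adding post-intervention months does not help.

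The loss cannot be repaired later, because an analysis plan cannot add prospectively registered baseline months once case-finding has begun. At stake is whether WP3 can say that detection raised the use of any service type beyond what was already happening.

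A second, conditional risk applies to the WP2 district. A register timed only to WP3 case-finding may open after HSAs and facility staff there have been trained and have used the system.

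**Working it through.** **Inputs.** From the article: monthly totals, a minimum of 3 pre-intervention months, segmented linear regression, three districts. Assumed, because the article gives no values: 12 post-intervention months, independent errors, two-sided alpha 0.05, 80% power. Results are in units of sigma, the monthly residual SD, for which there is no document figure. The article has no calculation of its own to reproduce here; sufficiency is asserted.

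**Model.** Intercept, pre-slope, level change and slope change. This is equivalent to two straight lines with a common residual variance. Number the months so that the first post-intervention month is t = 0; the n pre-months are then t = −n to −1, and post-month 6 is t = 5.

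**Step 1, pre-slope.** SE = sigma/√Sxx, with Sxx = n(n² − 1)/12.
- n = 3: Sxx = 2, SE = 0.71 sigma per month
- n = 6: Sxx = 17.5, SE = 0.24
- n = 12: Sxx = 143, SE = 0.084

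**Step 2, effect against the projected line at time t.** Variance/sigma² = 1/n + (t − mean pre-time)²/Sxx(pre) + 1/12 + (t − 5.5)²/143.

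At post-month 6 (t = 5):
- n = 3: 1/3 + 7²/2 + 1/12 + 0.5²/143 = 24.92, SE = 4.99 sigma. Of the 24.92, 24.5 comes from the pre-slope alone.
- n = 12: 1/12 + 11.5²/143 + 1/12 + 0.5²/143 = 1.09, SE = 1.05 sigma

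For the immediate level change (t = 0):
- n = 3: 1/3 + 2²/2 + 1/12 + 5.5²/143 = 2.63, SE = 1.62 sigma
- n = 12: 1/12 + 6.5²/143 + 1/12 + 5.5²/143 = 0.67, SE = 0.82 sigma

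**Step 3, detectable change.** From the noncentral t distribution. Residual df are n + 12 − 4 for one series. For three districts pooled with separate intercepts and common slope and change terms, they are 3(n + 12) − 6, and each SE is divided by √3.

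| Pre-months | df, one (pooled) | Month-6 effect, one (pooled) | Immediate level change, one (pooled) |
|---|---|---|---|
| 3 | 11 (39) | 15.4 (8.3) sigma | 5.0 (2.7) sigma |
| 6 | 14 (48) | 6.3 (3.45) sigma | 3.25 (1.8) sigma |
| 12 | 20 (66) | 3.1 (1.7) sigma | 2.4 (1.35) sigma |

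Going from 12 to 3 pre-months costs about five-fold at month 6 (15.4/3.1) and about two-fold for the immediate change (5.0/2.4). With 6 rather than 12 post-months, the three-point figures for one series become 17.7 and 5.9 sigma.

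**Step 4, level only, no trend term.** With 3 pre- and 12 post-months the SE of the difference in means is √(1/3 + 1/12) = 0.65 sigma. That precision comes entirely from assuming a flat series. The two periods have mean times −2 and 5.5, so an underlying trend of b per month would add 7.5b to the apparent effect.

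**Step 5, autocorrelation.** Simulated AR(1) errors with correlation 0.3 and 0.5, analysed by ordinary least squares, gave false-positive rates for the level change of about 6% with 3 pre-months, against 12% and 20% with 12.

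**The case against.** Three months is a floor. Under a sequential roll-out later districts may have longer registers, and Table 3 already names a possible source of earlier data. This stands as a possibility, so the figures above describe the least favourable case the text permits. Nothing commits to more, however, and the floor itself is called sufficient.

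Month 6 is also the harsher contrast. For the immediate level change the penalty is about two-fold. The Introduction says most people with psychosis in Malawi receive neither drug nor psychosocial treatment, so a large jump from a low base is plausible. This stands too: a reader might infer that the result will be uninterpretable, but the figures do not support that. The failure is confined to the beyond-trend claim.

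Two further inferences should be resisted. One is that a single residual degree of freedom makes spurious significance likely. That count belongs to a line fitted to the three pre-points alone; the planned model has 11 df in one series and 39 pooled. In the simulation three pre-points inflated false positives less than twelve did. The other is that the WP2 district's baseline is certainly contaminated. The article does not say how long after the WP2 test WP3 begins there or whether detection continues in between, and the start of case-finding in that district could be read as covering the WP2 test. Any carry-over is of unknown size and would probably raise the baseline.

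How seasonality and autocorrelation are modelled can be left to an analysis plan and is not faulted here. That three points carry almost no information on either remains true.

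**Conclusion.** The concern holds for the trend-based test. The guaranteed baseline does not support a conclusion about an increase beyond the pre-intervention trend, even with three districts pooled on a common slope (8.3 sigma detectable at post-month 6, against 1.7 with 12 baseline months). A large immediate jump remains detectable. The WP2 point is a risk to be managed, not an established fault.

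These sizes rest on 12 post-intervention months, independent errors and a linear trend, none of which the article states. Without a monthly SD they cannot be turned into numbers of contacts.

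The consequence is limited to the WP3 service-utilisation result and to the comparison with patient-reported service use in the Economic analysis. The WHOQoL primary outcome and its sample size are untouched. This should be put right before case-finding starts, but it is not critical to the trial's main conclusion.

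**What to change.** 1. Open the paper registers in all three districts at the same time, before the first district starts, and before WP2 training in the WP2 district where that is still possible. Under the sequential roll-out, later districts then gain longer baselines and serve as concurrent comparison series.
2. Extend the baseline backwards from the district health data named in Table 3 where records allow, and state the look-back period. The longer series should be analysed with an allowance for autocorrelation.
3. Mark the WP2 test period in that district's series so that it is not treated as untouched baseline.
4. Where only about three pre-intervention points exist, report a change in level only, labelled as assuming no underlying trend, and drop the claim of an increase beyond pre-intervention trends.
5. Replace the statement that three months is sufficient with the number of baseline points expected in each district.

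The cost is earlier running of a paper register, some record extraction and a change of wording. No new participants are needed.

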#### Deployment of the prototype manual and procedures

The HSAs will deliver the agreed protocol. We will conduct in-depth interviews with 20 people diagnosed with psychosis to understand their experience of the process and their perspectives on the diagnosis. We will also repeat the baseline survey (done in WP1 and 2) alongside in-depth interviews and focus groups with the HSAs who have been through the training and deployment to understand their views of the process and psychosis.

#### Fidelity and feasibility

The fidelity and feasibility approaches and measures will be developed from ToC 1 & 2 roadmaps and formally considered in a structured way in ToC workshop 4 and 6. However, it is anticipated that the indicators identified in Table 4 below will form part of the feasibility testing structure. Both qualitative and quantitative measures will be taken to establish fidelity to the programme procedures. HSAs will be purposively selected across a range of levels of engagement with the detection intervention, gender, and years of experience.

**Table 4 pone.0293370.t004:** WP3 anticipated feasibility testing structure.

**Programme Procedures**	**Quantitative**	**Qualitative**
Numbers screened, eligible, consented, completed screening/diagnostic assessment	Research log	
Number who lack capacity	Research log	
Refusal rate	Research log	
Acceptability of procedure		In-depth interviews with subsample of 20 HSAs
The number who were diagnosed with psychosis	Research log	
Experience of process		In-depth interviews with a subsample of HSAs and 10 PWLE
The burden of assessment procedures	Duration of assessment	
Health Surveillance Assistants: changes in their views about psychosis detection and management	Repeat baseline survey	
Health Surveillance Assistants’ views about processes and tools	Enhanced survey with screening/diagnosis questions	

### WP4—Evaluation of the psychosis detection and management system

Given the ethical issues associated with randomised controlled trials in this context, in particular that a control group would equate to no care for some or even most people [40], we have opted for a sequential implementation (WP1, 2 & 3) and a quasi-experimental statistical evaluation of outcome (WP4). Intervention cohort studies without a control group have been shown to be beneficial when creating a control group is unethical [41]. This also has the practical advantage of allowing us to support strengthening primary care and the management by District Mental Health Teams of people with psychosis as we identify them in each district. It also allows for iterative improvement of the intervention, replicating what happens in routine settings. To address ’maturation’ effects (e.g., change in staff performance due to the evolution of clinical skills) and Hawthorne effects, we will employ a 12-month intervention and observation period. We will keep a log of any time-related changes in service delivery and integration into primary care during the process. This will allow us to closely monitor any secular trends, such as changes in local healthcare provision or MoH policies, that might impact upon delivery of intervention or outcomes. In addition, we will continue qualitative and quantitative data collection with the HSAs surveyed throughout to give us insight into potential mechanisms.

#### Activities

*Intervention cohort study without controls / pre-post sequential group design*. The analysis of individual outcomes will use appropriate descriptive statistics to present the outcome in each district as well as the overall statistic for all three districts. The outcome data will be stratified by health equity indicators (sex, age category, urban/rural residence) and by drop outs and loss to follow up. A sample size of 150 will be sufficient to detect a pre-post improvement of 20% overall (across the four sub-scales) of the WHOQoL primary outcome measure with a power of 90% (alpha = 0.05). The data will have a three-level structure with repeated outcomes measures collected with individuals clustered within three separate assessment centres. It is reasonable to assume that different data from people with psychosis in the same centres will be correlated and measurements on the same person even more highly correlated. To handle this data structure we will use Mixed Models (including fixed effects and random latent effects) using the appropriate model for the distribution of outcome. For the continuous scaled primary outcome WHOQoL, a linear mixed effect model will model change before and after intervention to estimate mean difference as well as the moderating effects of key health inequity measures (gender, urban/rural residence, socio-economic status) and process indicators (e.g. engagement with facility-based and community-based interventions).

The final selection of outcome measures for the evaluation will be informed by PWLE of psychosis and other stakeholders, and Theory of Change roadmaps (ToC 1; ToC 2; ToC 3; ToC5) inclusive of agreed indicators of success. Quality of life is a valued outcome for both psychosocial interventions and antipsychotic medication, and is therefore the current proposed primary outcome measure. The range of potential measures are indicated in Table 5 below with outcome measures carried out at baseline (WP3) and at 6 and 12 months (WP 4). This allows for the incorporation of other measures prioritised by PWLE and other stakeholders, such as food insecurity [42], and will give enough time for participants to engage with the innovation to investigate feasibility, fidelity, cost-effectiveness and outcomes.

**Table 5 pone.0293370.t005:** WP4 anticipated outcome measures.

**Focus**	**Measure used to capture focus**	**Baseline (WP3)**	**6 months (WP4)**	**12 months (WP4)**
Primary outcome PWLE				
Quality of life	WHOQoL	x	x	x
Health Economics				
Disability	DALYS (symptom data)	x	x	x
Quality of life	WHOQoL	x	x	x
Secondary outcome				
Duration of untreated psychosis	DUP	x	x	x
Symptom Severity	Positive and Negative Syndrome Scale (PANSS)	x	x	
Family Burden	Family Burden Interview Schedule (FBIS)	x	x	
Health and disability	WHO Disability Assessment Schedule (WHODAS)	x	x	

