#### Activities

The key activities in WP3 will be to pilot the prototype manual and procedures of the psychosis detection and management system to N = 268 people to identify an anticipated N = 150 who screen positive for psychosis. This will be carried out sequentially, district by district, in the two districts involved in WPs 1 and 2 (Salima and Chiradzulu) and a third district (Ntcheu), which is equidistant between the others. The key informants in this WP are PWLE and their families, formal and informal caregivers, traditional and religious healers, HSAs, and clinic staff in Primary Health Centre and District Mental Health Teams. A process of engagement needs to be developed in the new Ntcheu district involved in WP3. This will be completed through ToC 6 workshop with PWLE and their families, and the other stakeholders above. Table 3 below gives an overview of WP3 activities.

**Table 3 pone.0293370.t003:** WP3 piloting of the psychosis detection and management system in 3 districts.

**Research questions**	**Methods**	**Key informants/participants**	
		**Community**	**Healthcare**
*What are the contextual adaptations required to implement the psychosis detection and management system in Ntcheu*?	ToC workshop 6 (n = 20 in Ntcheu)	People with lived experience Family/caregivers Traditional Healers Religious Healers	HSAs PHC staff DMHT staff Government Rep
*To what extent can HSAs trained in the psychosis and management tool accurately detect and refer people with psychosis to further care*?	Validation study (n = 268 screened)	People with possible psychosis	**-**
*Can the psychosis detection and management tool be delivered with fidelity by HSAs*?	Fidelity assessment (n = 60)	-	HSAs
*How did people with psychosis experience the detection and management process and what are the views of their diagnosis*	Qualitative interviews (n = 20 across three districts)	People with psychosis	-
*How did HSAs experience the detection and management process*? *How have their views on people with psychosis have changed*?	Qualitative interviews (n = 20 across Salima and Ntcheu)	-	HSAs
*What is the impact of the psychosis management and detection tool on service utilisation*?	Review of district health data	-	-

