#### Validation study

A power calculation, using Python, identified that we will need to screen 268 people with ‘possible’ psychosis to identify 162 ‘true positives’ to have at least 80% power (alpha 0.05) to detect a change percent value of specificity of the diagnostic tool from 80% to 90%. Initial case-finding of people with ‘possible’ psychosis will result from awareness-raising in the community and from training HSAs. People with possible psychosis will then be assessed by HSAs using the screening tool. All people who are considered to have psychosis based on the screening assessment (‘probable’ psychosis) and a random sample of screen negatives will undergo the gold standard diagnostic assessment administered by the RAs. The RAs will be masked to the outcome of the screening test. The gold standard diagnosis will include any diagnosis within the ‘schizophrenia or other primary psychotic disorders’ section of ICD-11, and affective psychosis, but will exclude organic or substance-induced psychoses. We will investigate sensitivity, specificity, positive and negative predictive values. The key concerns are to minimise false positives of a definitive psychosis diagnosis and to detect those with ongoing (not brief) psychosis that would benefit from an intervention that can be provided. We will use multivariate analyses to investigate possible predictors of inaccurate diagnosis (e.g. gender, educational level, age) to inform further implementation.

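### The 150 behind the 90% power for WHOQoL is the number expected to screen positive at entry, so the stated power is unsupported for the smaller number who will have follow-up

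*Protocol article*

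**What the plan says.** WP4, Activities, gives the sample size for the primary outcome: "A sample size of 150 will be sufficient to detect a pre-post improvement of 20% overall (across the four sub-scales". The sentence ends with the error rates: "WHOQoL primary outcome measure with a power of 90% (alpha = 0.05". It does not say whether the 20% is relative, absolute or standardised, and it gives no SD or time point. It also does not say whether the 150 are enrolled or analysed.

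WP3, Activities, uses the same number for people entering: "N = 268 people to identify an anticipated N = 150 who screen positive for psychosis". Baseline outcomes are taken in WP3, and the primary outcome is measured again at 6 and 12 months (Table 5).

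Just before the power statement, the article plans to break outcomes down by several factors: "sex, age category, urban/rural residence) and by drop outs and loss to follow up". Loss to follow-up is therefore expected. Just after it, the data are described as a three-level structure: "repeated outcomes measures collected with individuals clustered within three separate assessment centres". Mixed models with fixed and random effects are to handle this.

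Validation study gives another yield from the same 268: "we will need to screen 268 people with ‘possible’ psychosis to identify 162 ‘true positives". Its calculation is framed around specificity: "to detect a change percent value of specificity of the diagnostic tool from 80% to 90" percent. WP3, Activities, says the psychosocial interventions are for people who screen positive. The article does not say whether those without a confirmed diagnosis stay in the WP4 cohort.

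**The concern.** A pre-post contrast needs people with at least one follow-up measurement. Here the number expected to enter is also the number on which the power rests, in a paragraph that expects some to be lost. The two can agree only if nobody is lost or if 150 already holds a margin that is not stated.

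Two related matters affect the same analysis. The article gives two incompatible yields from one group of 268 people, 150 screen positives and 162 true positives, so the size of the WP4 cohort is unclear. The analysis also treats three centres as a level of the data. Three units give 2 degrees of freedom for a centre-level variance. The centres are not exchangeable either, because roll-out is sequential and the WP4 introduction and the Discussion both say the intervention is improved as it proceeds.

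At stake are the credibility of the power claim for the primary outcome and how far the estimated change can be generalised beyond the three districts.

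**Working it through.** **1. Can 150 be reproduced?** For a within-person change, n = ((1.96 + 1.282) × SD of change / difference)², two-sided alpha 0.05 and 90% power. With no SD, baseline mean or definition of the 20%, it cannot. Solving backwards:

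- Standardised change detectable with 150: 3.242/√150 = 0.265.
- If the 20% is relative to the baseline mean, the implied SD of change is 0.20/0.265 = 0.756 of that mean. On a 0-100 scale with an assumed baseline mean of 50, that is about 38 points.
- If the 20% meant 0.20 SD, n = (3.242/0.20)² ≈ 263, and 150 would give about 69% power. That reading does not yield 150.

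**2. If 150 is the exact requirement.** Power(n) = Φ(3.242 × √(n/150) − 1.96). Detectable improvement at 90% power = 20% × √(150/n). The loss rates are assumptions; the article gives none.

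| Loss | n followed | Power | Detectable at 90% |
|---|---|---|---|
| 0% | 150 | 90% | 20.0% |
| 10% | 135 | 87% | 21.1% |
| 20% | 120 | 83% | 22.4% |
| 30% | 105 | 77% | 23.9% |

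These count only complete cases. A mixed model that keeps people seen at 6 but not 12 months would lose less.

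**3. If 150 is not the exact requirement.** Assume a 0-100 scale and a 20% relative change:

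- Mean 50, SD of change 15: (3.242 × 15/10)² gives 24 people.
- Mean 40, SD of change 25: (3.242 × 25/8)² gives 103 people.
- Mean 50, SD of change 40: (3.242 × 40/10)² gives 169 people.

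So 150 could be generous or short, depending on an SD the article does not state.

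**4. The two yields from 268.** 268 − 162 = 106. A one-sample test of specificity, 80% against 90% with 80% power, needs ((1.96√0.16 + 0.842√0.09)/0.10)² ≈ 107 non-cases, and 107.4/0.40 ≈ 268.6. This suggests that 162 is the number of cases among those screened. On that reading, non-cases who screen positive number 106 × 0.20 ≈ 21 at 80% specificity, or 106 × 0.10 ≈ 11 at 90%. Read literally, however, 162 true positives exceeds the 150 people expected to screen positive at all. The article does not settle which is meant.

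**5. The centre level.** In a within-person contrast a centre random intercept cancels and costs no power. Centre matters when the change itself differs between districts, and three districts give only 2 degrees of freedom to estimate that variation.

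**The case against.** The strongest reply is that the article calls 150 sufficient, not minimal. The back-solved SD of change, about three quarters of the baseline mean, looks large. With the assumed SDs of 15 to 25 and means of 40 to 50, 24 to 103 people would do, and even 105 completers would meet 90%. This stands. A reader might infer that the primary analysis will fall short of its stated power, but the documents do not show that. They show that the 90% is not supported for the number who will be followed.

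A reader might also subtract false positives from the 150 and treat the remainder as the analysed sample. The article does not support this. It gives specificity but no sensitivity, and nothing removes unconfirmed screen positives from the WP4 cohort. If 162 is taken literally as the cohort, there is a margin of 1 − 150/162 = 7.4%; power, if 150 is the exact requirement, is then about 89%, 85% and 80% at 10%, 20% and 30% loss.

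A reader might further infer a severe loss of power from clustering. That needs a district random effect on change, which the article does not specify.

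Finally, a condensed article may leave the SD, the attrition rate and model details to fuller documents. Their absence alone would not be a finding. What remains is in the text itself: one number serves as both entrants and powered sample, two yields conflict, and three centres are offered as a level of a mixed model. The article already plans to present each district and the overall result, which is part of the remedy.

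**Conclusion.** The point holds in a limited form. The 90% is attached to the number expected to screen positive at entry, while the same section expects losses, so it is unsupported for the analysis that will be done. If 150 is exact, power is about 87%, 83% or 77% at assumed losses of 10%, 20% or 30%, somewhat better if 6-month data are used. If the true SD of change is well below three quarters of the baseline mean, 150 has slack and the loss may not matter. The article cannot distinguish these cases.

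The 150 and the 162 need reconciling. A centre-level variance from three districts that receive a progressively improved intervention is not a sound basis for inference beyond them.

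**What to change.** - Define the 20% improvement and give the SD of change used.
- State the attrition expected, and restate the power or the detectable improvement for the number expected at follow-up. No extra enrolment is needed for this.
- Reconcile the 150 screen positives with the 162 true positives. Say whether 150 means screen-positive, confirmed or followed participants, and whether people without a confirmed diagnosis stay in the WP4 cohort.
- Fit a random effect for person only, with district and district-by-time as fixed effects. Report the three district changes and their average, and limit the conclusion to these three districts.

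The cost is protocol wording and one line of model specification. The stated power may become less favourable, and generalising beyond the three districts becomes a judgement, no longer a model result.
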